### **8.2.3 Analysis of tertiary endpoints**

#### **Baseline age and HSV-2 status as modifier of the hormonal contraception and HIV acquisition relationship**

The study team will use survival analysis methods that parallel the approach used in the analysis of the primary outcome to assess these tertiary objectives. For each objective, a PH regression model will be fit with contraception arm as covariates, incorporating interactions between baseline age category or HSV-2 status and method group. All interactions will be assessed at the two-sided 0.05 level of significance.

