### 3.3 Tertiary Objectives

- To evaluate whether age modifies the hormonal contraception and HIV acquisition relationship
- To evaluate whether HSV-2 status modifies the hormonal contraception and HIV acquisition relationship
- To evaluate early HIV disease progression among seroconverters randomised to DMPA, LNG implant, and copper IUDs

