### 3.6 Tertiary Endpoints

- HIV plasma viral load and CD4 count
- HIV infection by baseline age sub-groups  $\leq 24$  years versus  $> 24$  years
- HIV infection by baseline HSV-2 status

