## 4.4 Eligibility Criteria

### 4.4.1 Inclusion Criteria

To be eligible for the study a woman must meet all of the following criteria:

- 16-35 years of age

- ⊖ Previously pregnant 16 and 17 year olds, where permissible by national regulations and local IRB approval
- HIV-seronegative
- Wants to use effective contraception
- Is able and willing to provide written informed consent
- Agrees to be randomised to either DMPA, LNG implant, or copper IUD
- Agrees to use assigned method for 18 months
- Agrees to follow all study requirements
- Intends to stay in the study area for the next 18 months, and willing and able to provide adequate locator information
- If has had a recent third trimester birth, is at least 6 weeks postpartum at time of enrolment
- Is sexually active (has had vaginal sex within the last 3 months) or was pregnant within the last 3 months
- Agrees not to participate in studies of drugs or vaccines or any other clinical research study while participating in this study.

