#### **4.4.3 Inclusion of Adolescents 16-17 Years Old**

Young women 16 and 17 years of age who have previously been pregnant and where permissible by national regulations and local IRB approval will be invited to participate. The inclusion of this population is important for several reasons. In many countries in Sub-Saharan Africa women 16-17 years of age have high rates of HIV incidence and also need effective contraceptive options. Thus, we anticipate in many countries this population will make up an important part of the study population and the HIV outcomes. Moreover, as the study research question is of particular importance to this group and to make findings generalisable, they should form part of the study population. Finally, there is a possibility that the effect of some hormonal contraceptives on HIV risk is greater among younger (rather than older) women and this underscores the importance of their inclusion.

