**Table 2: Screening Visit Procedures**

| Component                            | Procedures                                                                                                                                                                                                                                                                                                                                                                                            |
|--------------------------------------|-------------------------------------------------------------------------------------------------------------------------------------------------------------------------------------------------------------------------------------------------------------------------------------------------------------------------------------------------------------------------------------------------------|
| Administrative and Regulatory | 

• Obtain written informed consent

• Assign Participant Identification number

• Assess eligibility

• Collect locator information

• Provide reimbursement

• Schedule next visit

                                                                                                                                 |
| Behavioural/Counselling       | 

• Contraceptive counselling, including contraceptive continuation on all study methods

• HIV/STI risk reduction, including condom use and provision

• HIV pre- and post-test counselling

                                                                                                                                              |
| Clinical                      | 

• Collect demographic information

• Obtain medical, contraceptive, reproductive history/data

• Measure height, weight, and blood pressure

• Conduct pelvic examination

• Screen for cervical cancer (optional –based on local standards of care and availability of treatment)

• Assess for risk of pregnancy

 |

|                   |        |                                                                                                                                                                                                                                                 |

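### Age modification is tested only with age cut at 24 years; a supplementary interaction with age in years would protect against a graded effect at almost no cost

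*Protocol*

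**What the plan says.** The objective in section 3.3 is general: "To evaluate whether age modifies the hormonal contraception and HIV acquisition relationship". Section 3.6 narrows it to "HIV infection by baseline age sub-groups $\leq 24$ years versus $> 24$ years". Section 8.2.3 then specifies a proportional hazards model "incorporating interactions between baseline age category or HSV-2 status and method group", and adds that "All interactions will be assessed at the two-sided 0.05 level of significance".

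Two other parts of section 8.2 touch on age. The subgroup paragraph lists it, but with descriptive 95% intervals and no test of modification. The cofactor paragraph leaves covariates to the SAP, but it concerns effects on the infection rate and not modification of the method effect.

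On the data, section 4.4.1 requires "16-35 years of age" and Table 2 includes "Collect demographic information" at screening. Age in years is not named as a data item, but both the eligibility limits and the ≤24 split require it to be known.

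**The concern.** The specified test gives a woman of 16 the same value as one of 24, and a woman of 25 the same value as one of 35. If the method effect changes gradually over the enrolled range, that throws away information. The test then has a greater chance of missing the gradient, and the result may be reported as no modification by age.

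The question matters to the design. Section 4.4.3 justifies enrolling 16–17-year-olds partly on the possibility that "the effect of some hormonal contraceptives on HIV risk is greater among younger (rather than older) women". An interaction test at this event count is already limited in power, so a further loss is worth avoiding when it can be avoided without new data.

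**Working it through.** **Inputs from the protocol.** 250 events per pairwise comparison (8.1); two-sided 0.05 for interactions (8.2.3); ages 16–35 (4.4.1). Incidence by age comes from section 4.2.1, using band midpoints per 100 woman-years: 2.5 at 15–19, 3.5 at 20–24, 2.0 at 25–29 and 1.75 at 30–34. The last is carried to age 35; using the 35–39 midpoint of 1.25 instead changes results by less than one point.

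**Assumptions, because the protocol gives no figure.** The age distribution at enrolment, the size of the modification and its shape.

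**The plan's own figure.** With a hazard ratio of 1.5, 10% dilution applied to the log hazard ratio and two-sided 0.04, the events needed are 4(2.054 + 0.842)² / (0.9 × ln 1.5)² = 252, and 250 events give 79.7% power. The stated 250 events and 80% power reproduce. The protocol states no power for the age interaction.

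**Information kept by the cut.** For a pairwise 1:1 comparison, the information on an interaction is about (events/4) × the variance of the modifier among events. If the effect is linear in age, the share the cut retains is r², the squared correlation among events between age and the indicator of age ≤24.

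With even enrolment over 16–35, weighted by incidence:
- Share of events at ≤24: 0.573, so the indicator's variance is 0.573 × 0.427 = 0.245.
- Mean age of events: 20.4 (≤24) and 29.8 (>24), a gap of 9.45 years. Variance of age: 29.8.
- r = 9.45 × √0.245 / √29.8 = 0.86, so r² = 0.73 and the loss is 27%.

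If women aged ≤24 enrol at twice the rate, r = 0.84, r² = 0.71 and the loss is about 29%. Other assumed age distributions, with and without incidence weighting, give:

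| Enrolment by age | Information lost |
|---|---|
| Even over 16–35 | 26–29% |
| Declining linearly with age | 26–36% |
| Bell-shaped, centred at 22–26 | 32–46% |

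**Power under a log-linear age effect.** R is the ratio of the average hazard ratio at ≤24 to that at >24. With even enrolment, z(cut) = ln R × √(62.5 × 0.245) = 3.91 × ln R, z(age in years) = z(cut)/0.856, and power = Φ(z − 1.96) + Φ(−z − 1.96). At R = 1.75, z is 2.19 for the cut and 2.56 for age in years.

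| R | Even: cut | Even: years | Young-heavy: cut | Young-heavy: years |
|---|---|---|---|---|
| 1.5 | 35% | 46% | 30% | 40% |
| 1.75 | 59% | 72% | 50% | 65% |
| 2.0 | 77% | 89% | 68% | 83% |

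The cost is about 10–15 points. A simulation with 250 events per pair and even enrolment agrees: 52% falls to 41%, and 87% to 75%. Under the bell-shaped distributions, where the test on years has 50–90% power, the cost is about 14–26 points. If the three-arm interaction is tested on two degrees of freedom, a 27–29% loss costs about 12–16 points over the same range.

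**Power under a step at 24/25.** Now the linear term is the poor approximation and z(years) = 0.856 × z(cut). With even enrolment, at R = 1.75 the cut has 59% power and age in years 47%; at R = 2.0, 77% and 64%.

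**Counting either test as a signal.** With both tests at two-sided 0.05 and correlations of 0.86 and 0.84, the chance under the null that at least one is significant is 7.4% and 7.5% per pairwise comparison. With the 46% loss the correlation is √0.54 = 0.73 and the rate is about 8.2%.

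**The case against.** The strongest reply is that nothing is inconsistent: objective, endpoint and model agree, the cut is prespecified, and section 8.2 describes itself as a summary to be followed by a detailed SAP. A supplementary continuous-age model is ordinary SAP content. The first part stands, and this is not an error in the plan. The second stands only in part. The protocol itself names the cut as an endpoint and fixes the form of the only test, so the choice was made here, even though an unseen SAP may add to it.

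A reader might infer that the protocol describes a gradient and then ignores it. The text does not support that. Section 4.4.3 contrasts younger with older women, which fits a step equally well. Section 4.2.1 concerns background incidence, not the method effect. It is not monotone over the enrolled ages, and its largest change between adjacent bands falls at 24/25. Section 2.1 cites evidence on women aged 18–24 against older women, which loosely supports the cut, and Appendix 5 treats under 25 as young.

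A reader might also infer that continuous age should replace the category, or that the loss is known to within a few percent. Neither follows. The cut wins under a step, and the protocol has no age distribution from which to fix the loss.

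**Conclusion.** The point holds as a cheap improvement. The protocol commits its only test of age modification to one shape, a step at 24 years, without evidence that the modification has that shape.

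Under a graded effect the loss is roughly 26–46% of the information. It costs about 10–15 points of power with near-even enrolment and a one-degree-of-freedom test, and more if ages cluster near the cut. These figures rest on assumed age distributions, a log-linear effect and the planned 250 events per pair. The direction is safe for any graded effect that is close to linear; the exact size is not. Under a step at 24/25 the cut is better by about 12–13 points at the ratios shown.

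It would go too far to say that an absence of modification should be concluded only when both tests are negative. That rule would raise the false-signal rate from 5% to about 7.5% per pairwise comparison. The matter is confined to a tertiary objective.

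**What to change.** In section 8.2.3:

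- Keep the ≤24 versus >24 interaction as the prespecified test at two-sided 0.05, with the two age-group hazard ratios for display.
- Add one supplementary interaction of method group with baseline age in years, linear, in the same site-stratified proportional hazards model. Report it beside the categorical result with its estimate and 95% confidence interval.
- Do not make the conclusion depend on both tests being negative. If either is to count as a signal, state the false-signal rate of about 7.5% per pairwise comparison, or adjust for it; halving the level to 0.025 for each test is simple and conservative.
- Confirm that age in years, or date of birth, is recorded.

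The cost is one sentence and one extra tertiary model on data that eligibility already requires. Prespecifying it matters, because the same model added once results are known would look post hoc.

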#### **Early HIV disease progression**

Log-transformed viral load (VL) and CD4 T-cell count data will be compared between contraceptive groups among women who seroconvert using mixed effects models to account for repeated measures on subjects. Analyses will be performed according to women's original allocated method and according to contraceptive method used at the visit prior to seroconversion. Summaries will include absolute VL and CD4 measures from the seroconversion visit onward, as well as change in VL and CD4 from the seroconversion visit.

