#### **4.6.6 Concomitant Medications**

Women on liver enzyme-inducing medications (Appendix 10) are not excluded from the study, however use of such medications will be documented. Sites will counsel women of the potential increased risk of pregnancy, and may recommend additional barrier protection. Other concomitant medications will not be documented.

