#### **5.4.8 HIV infection**

Sites will fully counsel participants who seroconvert and refer them to local HIV care providers for on-going care, including CD4 cell count and antiretroviral treatment according to local policy. Seroconverters will be asked to remain in the study until completion of the follow-up period in order to continue data collection relevant to secondary outcomes.

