### **5.13 Procedures for HIV Seroconverters and Ancillary Studies of Early HIV Disease**

Sites will continue to follow confirmed HIV seroconverters on the study schedule, with all procedures except on-going HIV serologic testing and related pre- and post-test counselling. Participants who seroconvert can continue their study contraceptive methods unless contraindicated[65]. Plasma HIV RNA and CD4 quantification will be obtained in the event of possible seroconversion at all subsequent quarterly visits and at the final study visit. Potential additional sample collection for studies of early HIV disease will be included, dependent on site capacity, participant consent, and availability of funding and are outlined in Appendix 8. Sites will fully counsel participants who seroconvert and refer them to local HIV care providers for on-going care.

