## **Appendix 10: Medications that may cause drug interactions with some study methods**

### **Antiretrovirals**

- Protease inhibitors
- NNRTIs

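### Viral load and CD4 after ART start enter the early-progression analysis, and the protocol does not secure the ART start data needed to separate them

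*Protocol*

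**What the plan says.** The objective in Protocol section 3.3 is "To evaluate early HIV disease progression among seroconverters randomised to DMPA, LNG implant, and copper IUDs", and the matching endpoint in section 3.6 is "HIV plasma viral load and CD4 count". Under Early HIV disease progression in section 8.2.3, log-transformed VL and CD4 are compared between contraceptive groups with mixed effects models. The comparison is made twice: by allocated method, and by the method in use at the visit before seroconversion. On the data to be used, the section states "Summaries will include absolute VL and CD4 measures from the seroconversion visit onward" and adds "change in VL and CD4 from the seroconversion visit". It does not mention ART.

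Section 5.4.8 has sites counsel seroconverters and "refer them to local HIV care providers for on-going care, including CD4 cell count and antiretroviral treatment according to local policy", and asks the women to stay in follow-up. Section 5.13 adds "Plasma HIV RNA and CD4 quantification will be obtained in the event of possible seroconversion at all subsequent quarterly visits" and at the final visit. The notes to Appendix 6 confirm that the first measurement is at seroconversion.

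Section 4.6.6 has sites document use of the liver enzyme-inducing drugs in Appendix 10, then says "Other concomitant medications will not be documented". Under antiretrovirals, Appendix 10 lists two classes only: "Protease inhibitors" and NNRTIs.

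**The concern.** Once a woman starts ART, her VL and CD4 reflect treatment as well as the course of early infection. The stated data window runs through that point without a limit, so the analysis does not isolate what the objective asks about.

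Two consequences follow. If treatment starts at the same pace in every group, treated values dilute a real difference between methods and add variance. If the pace differs between groups, the difference in treatment appears as a difference in disease progression.

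The choice of analysis could still be settled in the SAP. The recording rule is different, because the protocol itself fixes which drugs are documented. An analyst cannot censor at, or adjust for, an ART start that was never collected.

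**Working it through.** **1. How many women.** The analysis has no planned figure of its own, so the primary sample size serves to size the group. Inputs from section 8.1: two-sided alpha 0.04, 80% power, a 50% increase, and up to 10% dilution. Schoenfeld's formula with the log hazard ratio multiplied by 0.9 gives 4 × (2.054 + 0.842)² / (0.9 × ln 1.5)² ≈ 252 events per pair, which reproduces the planned 250. Expected seroconverters are 7,800 × 0.035 × 1.5 ≈ 410 with no loss of person-time, and 410 × 0.9 ≈ 369 with 10% lost. That is about 123 to 136 per arm.

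**2. How many measurements come after referral.** Visits with HIV testing are at months 3, 6, 9, 12, 15 and 18 (sections 5.7.2 and 5.7.3). Assume detection is equally likely at each. Measurements per woman average (6 + 5 + 4 + 3 + 2 + 1)/6 = 21/6 = 3.5. The share taken at the seroconversion visit is 6/21 = 29%; the other 15/21 = 71% come later. Every change value uses one of these later measurements.

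**3. What share could be on ART.** The protocol gives no time to ART, so this is a range. Assume exponential time to ART with median m months. With k quarters since detection, the post-ART share of all measurements is Σ (6 − k)(1 − 2^(−3k/m)) / 21, for k = 0 to 5.

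| Assumed median time to ART | Share of all measurements after ART start |
|---|---|
| 1 month | 68% |
| 3 months | 52% |
| 6 months | 37% |
| 12 months | 23% |
| 24 months | 13% |
| no ART | 0% |

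**4. Effect on the comparison.** Let D be the fall in log10 VL on ART (assumed 2 to 3) and d the difference between groups in the share of measurements on ART. In a simple average of all values, the false difference is D × d. For d = 0.10 this is 2 × 0.10 = 0.2 to 3 × 0.10 = 0.3 log10. For d = 0 it is zero. With equal uptake, and assuming no difference between methods once on ART, the same average keeps 1 − q of the true difference, where q is the share on ART: from 1 − 0.13 = 87% to 1 − 0.68 = 32% over the range in step 3.

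**5. What is recorded.** Setting sections 4.6.6 and 8.2.3 side by side:
- A regimen containing a protease inhibitor or an NNRTI is documented as used. No start date is expressly required.
- A regimen with neither falls under the rule that other medications are not documented.
- Section 5.9 puts use of HIV prevention strategies on case report forms, which is not treatment of seroconverters.
- The schedule in Appendix 6 has no ART item.

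**The case against.** The strongest reply is that section 8.2 calls itself a summary, with a detailed SAP to follow. Section 8.2.3 names a model and what the summaries include; it does not rule out censoring or adjustment for ART. That is right, and silence on an ART rule would not alone be a finding. It does not answer the recording gap.

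A second reply is that allocation is randomised, the quarterly visits are the same in all arms, and the referral rule is the same for all. Nothing in the protocol shows that ART uptake differs by arm. This also stands: bias by arm is a risk, not a fact. The protection is incomplete, however. The comparison is among women who seroconverted, which happens after randomisation, and the second analysis groups women by method used, which is not randomised.

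Third, there are partial sources. Listed classes are documented, quarterly VL would often show that treatment had begun, and section 11.10 calls for a final care plan for each seroconverter. A reader might therefore go too far in inferring that the gap is beyond repair. These sources soften it, but they do not supply a start date and regimen for everyone.

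A reader might also infer that the analysis measures ART uptake instead of progression. The protocol does not support that. The value at the seroconversion visit precedes referral, absolute values are reported as well as change, and referral under local policy does not mean that every woman starts treatment.

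**Conclusion.** The concern holds in a limited form. As written, section 8.2.3 includes values after ART start, and section 4.6.6 with Appendix 10 does not secure the data that any later correction would need. A SAP could not fully repair this.

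The size cannot be fixed from the protocol. The 0.2 to 0.3 log10 figure rests on an assumed ART effect of 2 to 3 log10 and an assumed 10-point imbalance. The 13% to 68% post-ART share rests on assumed median times to ART of 24 months down to 1 month. The dilution figures are for a simple average, and the planned mixed model would weight the values differently. For the same reason, a loss of information computed by treating values as independent draws from treated and untreated women would not describe the planned analysis, and none is claimed here. No effect on CD4 is quantified.

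The primary and secondary analyses are untouched.

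**What to change.** In section 4.6.6, require the ART start date and regimen for every seroconverter, whatever the drug class. In section 8.2.3, add an analysis of VL and CD4 limited to values before ART start, keep the all-values summary beside it, and describe time to ART start by arm.

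The cost is one case report form item for about 370 to 410 women and a short addition to the analysis text. The pre-ART analysis will use fewer values. If local policy ties ART to CD4, which the protocol does not say, stopping at ART start would depend on the outcome itself. That is a reason to report both analyses and not to replace one with the other. The change concerns recording and analysis only and leaves clinical care as it is.
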